#### Changing from control to intervention

During the intervention period every patient of the control group has the option to cancel the participation and to register to the intervention group. All data collected so far are assigned to the control group.

#### Additional data

The questionnaires given to the intervention patients include items to describe the use of the intervention modules.

To evaluate the impact of PIKKO on healthcare costs, all the participating health insurance companies provide pseudonymous patient data. These data are collected from three groups: control group, intervention group and a second control group of patients who meet the inclusion criteria but do not participate in PIKKO.

Furthermore, pseudonymous usage data from the oncological knowledge database are analyzed and interviews with PN and enrollment persons are carried out.

The patients agreed to the collection of these data during the inclusion. Then, these data is collected without further contact to patients and in concordance with the data protection act.

### Sample size calculation

The three participating health insurance companies have a potential of 325,000 insured persons in the Saarland and their averaged prevalence of cancer (ICD-10-diagnosis groups C00-C97 or D45-D48) is 6.532%. Thus, the study population included (rounded up) 22,000 patients.

The financing of the PIKKO supply concept was calculated for a maximum of 1.800 patients per group, 3.600 patients in total. That means that 1.800 participants of the intervention group can benefit from the PN and the other intervention modules.

To evaluate the PIKKO intervention only 676 participants (338 per group) of the patient questionnaires are required to the statistical analyses. This number of cases was calculated with the program GPower version 3.1.7 [41]. The calculation is based on an expected effect of d = 0.25 for a two-sided t-test with same sized comparative groups, a level of significance of α = 0.05 and a power of 1-β = 0.9. The t-test refers to the primary outcome. We assumed that 338 patients would drop out and added this amount to the total number of included patients. As a consequence, the recruiting aim was *N* = 1014 = 676 + 338 patients (per group 507 = 338 reaching the end point + 169 dropout). The expected dropout rate was 33.3% regarding the baseline (338 of 1014) or respectively 50% regarding the patients reached the endpoint (338 of 676).

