### Study setting

To evaluate this health care project, three participating statutory health care insurance companies (IKK Südwest, Techniker Krankenkasse, Knappschaft) work together to offer PIKKO to their insured cancer patients in the Saarland, which is the second smallest state in Germany (997,000 inhabitants). About 80 physicians (clinicians and practitioners, various specializations) in about 25 cities (different population sizes) agreed to recruit participants. The intervention is performed by specially trained PN who are located in clinical or outpatient settings.

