### Recruitment

To recruit physicians to participate in PIKKO, the consortium leader (IKK Südwest) organized internal (invitations to the IKK Südwest) and participated in external (health-related congresses and similar) information events. They are addressed to all physicians of different specialization that are involved in care of cancer patients: oncologists, gynecologists, urologists, general practitioners, internists, and other. The participating hospitals, clinics, and medical practice must sign a study contract to participate in the supply concept PIKKO and to recruit patients. The enrollment is conducted by physicians or trained medical staff e.g. a nurse.

For the recruitment of PN, mailings were made to all participating hospitals, clinics and practices. Up to ten persons can be trained with a two weeks course by the German Cancer Society. Target group are people who already work in the field of cancer-related health care such as oncological nurses, social workers or other non-medical staff of an oncological outpatient clinic or oncological department of a hospital.

The patients are recruited in various ways. Firstly, they can be addressed directly while attending a medical consultation (outpatient or inpatient) as long as they show the inclusion criteria. The enrollment is carried out directly. Secondly, a landing page at the internet serves as a contact point to patients who hear about PIKKO via mass media such as newspaper articles and radio program or on various events about cancer [27]. The potential participant is using a contact form and receives a phone call by his/her health insurance company. Eligibility criteria are checked and a local enrollment is arranged. Thirdly, health insurance companies can recommend their members to attend the study. The enrollment is carried out by post. And fourthly patients can actively ask their physician, statutory health insurance, the German Cancer Society, the Cancer Society of the Saarland or the evaluator. In this case the potential participant will be led to a local enrollment person.

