### Data management

#### Data organization

Contact and process information are saved in a database which is programmed with Microsoft Access especially for this evaluation (names; address; telephone number; allocation; contact events, outgoing or incoming of questionnaires; date of enrollment; date of dispatch; date of fill out; enrollment person; PN; withdrawal; data entry). The database keeps track the patients’ timeline and allows intervening if the time interval between the patient questionnaires becomes too large (algorithm and alerts). In addition, the database enables the cooperation partners to be kept up to date in terms of recruitment and study process (reports and summaries). Access is multiple times secured for privacy reasons.

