### Statistical methods

Characteristics of control and intervention groups (e.g. age, sex, education, family situation, partner situation) will be analyzed with descriptive statistics. Since no randomization is made for ethical and research practical reasons, univariate tests are used to determine which of the above mentioned characteristics differ between the two groups. Ideally there are no significant differences between the two groups. In the case of significant differences we will compute propensity scores using the corresponding pre-treatment variables. Then, we will apply in the subsequent analyses propensity scores as stabilized regression weights to reduce bias caused by different group characteristics.

The main hypothesis of an intervention effect on psychological and physical health, self-efficacy, health care costs etc. will be proofed by the comparison of averages of intervention and control group (resp. t-tests). To estimate the corresponding regression adjusted group means we will use growth curve models. Furthermore, we will conduct subgroup analyses to identify conditional treatment effects.

For dropout analysis we will conduct a logistic regression with dropout as criterion and group assignment and baseline variables as predictors applying the regression weight mentioned above. For the time-to-event analysis we will conduct a Cox regression.

The level of significance will be α = 0.05. To validate our analyses, we will conduct the analyses with imputed missing data and without imputation.

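### The 0.9 power holds only for independent, unweighted patients; neither the calculation nor the named t-test allows for at most ten navigators treating the whole intervention arm

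*Protocol article*

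**What the plan says.** The Sample size calculation section fixes the whole basis of the figure. "The calculation is based on an expected effect of d = 0.25 for a two-sided t-test with same sized comparative groups", with "a level of significance of α = 0.05 and a power of 1-β = 0.9". From this it concludes that "only 676 participants (338 per group) of the patient questionnaires are required to the statistical analyses". The only inflation is for dropout: "The expected dropout rate was 33.3% regarding the baseline (338 of 1014").

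On delivery, the Study setting section says that navigators perform the intervention, and the Recruitment section says "Up to ten persons can be trained with a two weeks course by the German Cancer Society". The Intervention section has the navigator open access to the database, and arrange the specialised counselling. Controls have no navigator. Enrolment draws on "About 80 physicians (clinicians and practitioners, various specializations) in about 25 cities", with further routes through the insurers, including enrolment by post.

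On analysis, the Statistical methods section tests the main hypothesis by comparing group averages with t-tests and uses growth curve models for the adjusted means. If baseline characteristics differ significantly, it applies "propensity scores as stabilized regression weights". The Limitations section announces propensity scores without that condition. Navigator, physician or site is nowhere named as a level of the analysis. The tracking database does record the navigator: its field list includes "date of fill out; enrollment person; PN; withdrawal; data entry".

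**The concern.** Patients advised by the same navigator share that person's skill, style and local setting, so their six-month SF-12 mental scores may be correlated. The article itself counts the navigator's own experience, talent and empathy among the qualifications for the role, which makes a correlation of exactly zero hard to defend. With roughly 34 patients per navigator, even a small correlation inflates the variance of the intervention mean. A patient-level t-test does not see this.

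Two things are at stake. First, 0.9 is then an upper figure for the t-test as calculated, not the figure to expect. Second, and more important, a test that ignores navigator rejects a true null hypothesis more often than 5% of the time. The article wants to use a positive result to recommend rollout across Germany, that is, to navigators who were not in the study. The standard error therefore has to include variation between navigators.

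Weighting is a smaller, separate matter: unequal propensity weights reduce the effective sample size, and the calculation makes no allowance for that either.

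**Working it through.** **Inputs from the article:** d = 0.25 (SD = 1), two-sided alpha 0.05, 338 analysed per group, at most 10 navigators, about 80 physicians.

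**Assumed, because the article gives no value:** navigator ICC 0.01, 0.02 or 0.05; variance inflation from weights 1.1, 1.2 or 1.5; baseline to six-month correlation r = 0.5; equal caseloads.

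**1. The plan's own figure.** The noncentral t solution is 337.2, rounded up to 338. Power at 338 per group is 0.9007. Dropout of one third gives 338 / (2/3) = 507 per group and 1014 in total. All stated figures reproduce.

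**2. Navigator clustering, intervention arm only.** Mean caseload m = 338/10 = 33.8, and larger with fewer navigators. The design effect is D = 1 + (m − 1) × ICC = 1 + 32.8 × ICC in the intervention arm and 1 in the control arm.

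- Power = Φ(0.25 / √((D + 1)/338) − 1.96).
- If navigator is ignored, the true SE is √((D + 1)/2) times the naive SE, and real alpha = 2 × (1 − Φ(1.96 / √((D + 1)/2))).

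For example, at ICC 0.02, D = 1.656, SE = √(2.656/338) = 0.0886, and 0.25/0.0886 = 2.82. Power is Φ(2.82 − 1.96) = 0.805. The SE ratio is √1.328 = 1.152, so real alpha is 2 × (1 − Φ(1.701)) = 0.089.

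| Navigator ICC | D | Power (normal) | Power (Satterthwaite df) | True / naive SE | Real alpha if ignored |
|---|---|---|---|---|---|
| 0 | 1 | 90.1% | – | 1 | 5.0% |
| 0.01 | 1.328 | 85.4% | 82.8% (27.2 df) | 1.08 | 6.9% |
| 0.02 | 1.656 | 80.5% | 77.1% (22.9 df) | 1.15 | 8.9% |
| 0.05 | 2.640 | 67.3% | 62.2% (17.0 df) | 1.35 | 14.6% |

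**3. Weights, if used.** With variance multiplier w in both arms, power = Φ(0.25 / √(2w/338) − 1.96). This gives 87.3%, 84.3% and 75.6% at w = 1.1, 1.2 and 1.5. Combined with navigator clustering at w = 1.2, it is 78.5% at ICC 0.01 and 73.1% at ICC 0.02.

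**4. Baseline adjustment.** At r = 0.5 the residual variance factor is 1 − 0.25 = 0.75. Two cases bound the navigator part: adjustment leaves navigator variance untouched (variance sum 2 × 0.75 + 32.8 × ICC), or reduces it in proportion (0.75 × (D + 1)).

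| Navigator ICC | Variance sum, untouched / proportional | Power without weights | Power with w = 1.2 |
|---|---|---|---|
| 0.01 | 1.828 / 1.746 | 92.5% / 93.6% | 87.4% / 88.8% |
| 0.02 | 2.156 / 1.992 | 87.9% / 90.3% | 81.5% / 84.4% |
| 0.05 | 3.140 / 2.730 | 73.7% / 79.4% | 65.8% / 71.9% |

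Adjustment does not cure the alpha. If navigator variance shrinks in proportion, the SE ratio, and so the real alpha, is as in step 2. If it is untouched, the naive SE falls while the navigator part stays. At ICC 0.01 the ratio becomes √(1.828/1.5) = 1.104 and real alpha about 7.6%. At ICC 0.02 it is √(2.156/1.5) = 1.199 and about 10.2%.

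**5. Physicians.** If all patients came through the 80 physicians, there would be 338/80 = 4.2 per physician per arm. Treated as independent between arms, with design effect 1 + 3.2 × ICC in both, power is 89.2%, 88.3% and 85.5% at ICC 0.01, 0.02 and 0.05. This part is minor.

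**The case against.** The strongest reply has four parts.

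*The calculation is right for the test it names.* This stands. The fault is an unstated independence assumption, not an arithmetic error.

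*The magnitudes are assumed.* This also stands. The article supplies neither an ICC nor a weight variance. Some components, such as the database content, the ring folder and the courses, come from central providers, so nothing points to a high navigator ICC. The 0.05 row marks the end of a range and is not an expectation.

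*The standard errors are not fixed.* A reader might infer that the planned standard errors are too small. The article does not support that as a general statement. It fixes no variance estimator for the growth curve models, which could carry a navigator effect or robust errors, and an analysis plan that is not shown may say so. What stands is narrower: the t-test is the only test named for the main hypothesis and the basis of the sample size, and applied as named it ignores navigator.

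*Power may be adequate after all.* A reader might also infer that the trial certainly falls short of 0.9. That is not supported either. SF-12 is measured at baseline, and with adjustment several scenarios in step 4 reach or exceed 0.9. Nor is a weighting loss certain: Statistical methods makes weights conditional on significant differences, while Limitations does not, and the two should be reconciled.

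Extending the point to physicians or facilities adds little. The loss is small, stable physician effects partly cancel if the same physicians recruit in both periods, and some patients enrol by post. Facility is also not among the listed database fields; enrolment person is.

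**Conclusion.** The concern holds in a limited form. The stated 0.9 is a best case for independent, unweighted patients, and the navigator structure described in the same article is left out of both the calculation and the named test. For the t-test as calculated, any positive navigator ICC or any variable weights put power below 0.9: about 85% to 80% at ICC 0.01 to 0.02 without weights. Net power below 0.9 after baseline adjustment is plausible but not proven; at r = 0.5 without weights it is about 92% to 94% at ICC 0.01 and about 88% to 90% at ICC 0.02.

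The alpha problem is the firmer part. It is conditional on navigator being ignored, but then a nominal 5% test runs at about 7% to 9% at ICC 0.01 to 0.02, and baseline adjustment does not remove the excess. All of these figures rest on the assumed ICC, weight loss and correlation, on ten navigators and on equal caseloads. The change is worth making, because the conclusion is meant to carry over to new navigators.

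**What to change.** - Replace the plain t-test in the primary comparison by a partially nested model: a navigator random effect in the intervention arm only, with small-sample degrees of freedom (Satterthwaite or Kenward–Roger). Adjust for baseline SF-12. The navigator identifier is already recorded in the tracking database.
- Present 0.9 as the independent, unweighted best case. Add a short sensitivity table for 338 per group over navigator ICC, weight loss and baseline adjustment, with the ICC values labelled as assumptions.
- State in one place whether propensity weights are conditional or always used, so that Statistical methods and Limitations agree.
- Optionally, add a term for the enrolling person as a sensitivity analysis.

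The cost is a somewhat more complex primary model, wider intervals and a less favourable stated power. No extra enrolment is needed, and recruitment had closed in any case. With the number of navigators fixed, extra patients would also help little at higher ICC: at ICC 0.05 about 2057 analysed patients per group would be needed for 90% power without baseline adjustment.

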### Data collection methods

According to the four aspects of this evaluation, four different kinds of data are obtained from four different sources.

Up to five times the patients will be asked to fill out a set of questionnaires. The length of these sets varies between 12 and 20 DINA4-pages. With the length and the allocation, the content of the set differs too (see Table 1). Questionnaire sets of the intervention group are longer than of the control group because they included questions about the frequency of use and quality of PIKKO interventions. All questionnaire sets included the six validated questionnaires SF-12 (main outcome, HRQoL, Cronbach’s α = 0.76–0.90 [29]), GSE (self-efficacy, Cronbach’s α = 0.80–0.90 [33]), PHQ-9 (depression, Cronbach’s α = 0.88 [35]), GAD-7 (anxiety, Cronbach’s α = 0.89 [37]), Qualiskope-A (patient satisfaction in health care, Cronbach’s α = 0.87–0.94 [40]) and HLS-EU-Q47 (health literacy, Cronbach’s α = 0.97 [39]). We chose the written form of patient survey because of the expected age structure of the patients. In 2013, the mean age of onset of cancer in Germany was 67.2 (female) and 68.3 (male) years [42]. In 2017, only 61% of people older than 65 used the internet privately [43], but the use of the internet is a prerequisite for online surveys. In a written survey, a much higher response rate is expected.

The second data source is data from the health insurance companies. Different types of values are summarized (see Table 2). These data are pseudonymized and cannot be matched with questionnaire data.

**Table 2 Tab2:** Additional pseudonymized secondary outcomes and time of measurement

Measure	Source	Time of measurement
Economic data		
Demographics	Statutory health insurance companies	6 months after closing recruitment separated in allocation groups
Diagnoses	Statutory health insurance companies	
Ambulatory costs	Statutory health insurance companies	
Stationary costs	Statutory health insurance companies	
Costs of psychological therapy	Statutory health insurance companies	
Medication costs	Statutory health insurance companies	
Days of inability to work	Statutory health insurance companies	
Oncological knowledge database		
Usage data: number of visits, visited subpages, printed content, online time	German Cancer Society	6 months after closing recruitment of the intervention group

Log files from “Mein PIKKO” are the third data type. This anonymous data will be provided from the German Cancer Society and based on the usage of the oncological knowledge database (see Table 2).

The last data types are telephone interviews carried out with PN and study physicians. These interviews focus on quality and implementation aspects of the PIKKO intervention.

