#### Secondary outcomes

Other measurements and supposed effects by the intervention are:
improvement of self-efficacy measured by the General Self-Efficacy Scale, GSE [33],reduction of psychological distress such as depression (measured by the Patient Health Questionnaire-9, PHQ-9 [34, 35]) or anxiety (measured by the General Anxiety Disorder, GAD-7 [36, 37]),improvement of health literacy measured by the HLS-EU-Q47 [38, 39],improvement of patient satisfaction in health care measured by the Qualiskope-A [40],lower health care costs such as ambulatory and stationary costs, medication costs, costs of psychological therapy,reduction of days of inability to work (DIW).

GSE, PHQ-9, GAD-7, HLS-EU-Q47 and Qualiskope-A are well validated [29, 33, 35, 37, 39, 40]. They are part of the patient questionnaire set which will be sent to the patients. Costs and DIW are identified from secondary data analysis from the three participating statutory health insurance companies.

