### Trial status

The study protocol was approved by the ethics committee of medical association of the Saarland at 2nd November 2017. The first patient of the control group was included on 23th November 2017. The control group was recruited till 31st October 2018. Since then till 31st March 2020 the intervention group was recruited. An extension of the recruitment period of the intervention group (from one year to one and a half year) was necessary due to the entry of a further statutory health insurance (AOK Rheinland-Pfalz/Saarland) in the summer of 2019.

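### Propensity weights built on questionnaire variables cannot be attached to the unlinked insurer records, so costs and days of inability to work lose the planned adjustment unless a separate score is fitted there

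*Protocol article*

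**What the plan says.** Under Secondary outcomes, the source of the economic endpoints is fixed: "Costs and DIW are identified from secondary data analysis from the three participating statutory health insurance companies". Under Data collection methods, these records are described as follows: "These data are pseudonymized and cannot be matched with questionnaire data".

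Statistical methods sets out the adjustment in three steps. First, "Characteristics of control and intervention groups (e.g. age, sex, education, family situation, partner situation) will be analyzed with descriptive statistics", followed by univariate tests for differences. Second, "In the case of significant differences we will compute propensity scores using the corresponding pre-treatment variables". Third, "we will apply in the subsequent analyses propensity scores as stabilized regression weights to reduce bias caused by different group characteristics". The next paragraph of that section includes health care costs in the main hypothesis, to be tested by comparing group averages, with regression-adjusted means from growth curve models. It makes no exception for insurer data. Limitations names propensity scores as the compensation for not randomizing.

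Table 2 lists demographics and diagnoses among the insurer variables and times the extraction at "6 months after closing recruitment separated in allocation groups". Trial status gives control recruitment as 23 November 2017 to 31 October 2018. For the other group it says: "Since then till 31st March 2020 the intervention group was recruited".

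**The concern.** A weight belongs to one patient. If it is estimated from questionnaire answers, it can be used on a cost record only when the two can be linked, and the article rules that out. The adjustment in Statistical methods therefore cannot be carried out as written for costs and DIW whenever a questionnaire-only variable enters the score.

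The two enrolled groups come from different calendar periods, and participation was voluntary in both. Case mix and period can both differ, and the weights are the named protection against differences in patient characteristics. Lower direct costs are a stated expectation of the programme, so an unadjusted or differently adjusted cost contrast matters for how the result is read.

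A second, conditional matter is observation time. The two recruitment periods turned out unequal in length, so totals accumulated up to extraction would cover different amounts of time per patient.

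**Working it through.** **Linkage: the statements side by side**

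1. Cost and DIW outcomes: insurer records only (Secondary outcomes; Table 2).
2. Example characteristics for the score: age, sex, education, family situation, partner situation (Statistical methods). Age and sex would normally be part of insurer demographics, although Table 2 does not itemize them. Nothing in Table 2 indicates that education, family or partner situation is held there.
3. Use of the weights: subsequent analyses, with costs named in the next paragraph.
4. Linkage between the two sources: none (Data collection methods).

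From 1, 2 and 4, a weight containing any questionnaire-only variable has no counterpart in the cost file, so 3 fails for costs and DIW.

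Two further statements point the same way. Limitations says insurer data are collected from all included patients while questionnaires depend on their cooperation, so some cost records may have no questionnaire behind them. The second control group supplies only health care data (Trial design), so a questionnaire-based score is undefined for it.

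**Observation time: scenarios, not a plan figure**

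The article states no follow-up figure for costs, so there is none to reproduce. Its sample size does reproduce: the t-test solution for d = 0.25, two-sided α = 0.05 and power 0.90 is 337.2, hence 338 per group, and 338 / (1 − 1/3) = 507. This point does not touch it.

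Inputs are the recruitment dates in Trial status (intervention start taken as 1 November 2018) and the six-month rule in Table 2. Available time = extraction date − enrolment date. Under uniform accrual (an assumption), the mean is the midpoint of the range. One month = 30.4375 days.

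| Scenario | Control | Intervention |
|---|---|---|
| Recruitment length | 342 days = 11.2 months | 516 days = 17.0 months |
| Group-wise extraction (30 Apr 2019; 30 Sep 2020) | 181 to 523 days, mean 352 = 11.6 months | 183 to 699 days, mean 441 = 14.5 months |
| One common extraction (30 Sep 2020) | 23.0 to 34.2 months, mean 28.6 | 6.0 to 23.0 months, mean 14.5 |
| One year of recruitment per group, as in Participant timeline, group-wise extraction | about 6 to 18 months, mean 12 | about 6 to 18 months, mean 12 |

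Ratio of intervention to control, group-wise: 441 / 352 = 1.25. With one common extraction: 14.5 / 28.6 = 0.51. The ranges need no accrual assumption; the means do.

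The last control enrolled (31 October 2018) reaches 30 April 2019, and the last intervention patient (31 March 2020) reaches 30 September 2020. Six calendar months are therefore available for every enrolled patient on either reading, apart from death or switching.

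**The case against.** The strongest reply is that Statistical methods does not say the propensity variables must come from questionnaires. The list is introduced as examples, Table 2 places demographics and diagnoses inside the insurer data, and a score fitted separately there is compatible with the text. Growth curve models with regression-adjusted means are planned as well. This stands against a reading that a reader might infer, namely that no propensity weighting is possible and that costs will be compared as raw means. The documents do not support that. What remains is that the article describes one score, illustrates it partly with variables the insurers are not shown to hold, and applies it across unlinked sources without saying how.

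A reader might also infer that the extraction rule itself makes follow-up unequal between groups. It does not: with the planned year per group the two would match. The gap arises from the extension of intervention recruitment, or from reading Table 2 as a single extraction reported by group.

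Nor is a 25% bias established. An extraction date is not an analysis window, the Abstract speaks of a time course of costs, and the full plan may define a window. The figure needs uniform accrual, totals accumulated to extraction and group-wise extraction. Under a common extraction the direction reverses.

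Finally, costs and DIW are secondary outcomes, and the primary comparison is untouched. That also stands.

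**Conclusion.** The inconsistency holds in a limited form. Propensity weights that depend on questionnaire-only characteristics cannot be attached to the insurer records, so the adjustment described in Statistical methods, and relied on in Limitations, is not available for costs and DIW as written. This rests on the article's own statements and needs no numerical assumption. The size and direction of any resulting bias cannot be derived from the documents.

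On observation time, the supportable statement is conditional: if costs were compared as unstandardized totals up to extraction, the groups would not be comparable on either reading of Table 2. The mean would be 11.6 against 14.5 months with group-wise extraction, or about 28.6 against 14.5 with a common one. Nothing shown says that totals will be used in this way. The SF-12 analysis and the sample size are unaffected.

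**What to change.** State that costs and DIW have their own propensity model, fitted within the insurer data on the covariates held there:

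- age and sex;
- cancer diagnosis group and comorbid diagnoses;
- insurer, where both groups contain its members (Trial status reports a further insurer joining in summer 2019, after control recruitment had closed);
- costs and DIW before enrolment, if the data approval allows. Table 2 does not list these, so consent and data-protection cover must be checked first.

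Report covariate balance for this model separately, and acknowledge that education, family and partner situation remain unadjusted for these outcomes unless the insurers hold them.

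Define the comparison as the same fixed window after enrolment in every patient. The first six months is the longest window that every enrolled patient has by the Table 2 extraction time, and it matches the timing of the primary outcome. The enrolment form goes to the insurer (Participant timeline), so an index date should exist for both enrolled groups. Use person-time for deaths and for controls who switch to the intervention group. A control enrolled late in October 2018 could switch well before six months, and switching may be related to need, so the rule for it should be written down.

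The cost is a slightly larger insurer data request and some additional analysis. A six-month window also leaves later costs out of the main contrast. No change to the questionnaire analyses is needed.
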